**Control group (n=405)**

- Usual care (services)
- Welcome message
- No continuous follow up

Phase 2 follow up assessment at the end of 3^rd^ and 6^th^ month

**Main outcome:** Screening Uptake **Secondary outcomes:** Increased knowledge, attitude and intention to screening

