## 3.6. Study Variables

**3.6.1. Dependent variables**

- Breast screening behavior/ uptake (breast self-examination, mammography use, clinical exam)
  - 1. **Predictor variables: (modifying factors, experience and perceptions)**
- **Socio demographic**, socio-psychological and structural characteristics ( age, marital status, religion etc., general knowledge about breast cancer and screening, health motivation/values)
- **Socio-economic variable:** income, occupational status, wealth index
- **Past behaviors related to breast cancer and experience of screening (**knowing status of partner, screening experience).
- **Perceived susceptibility** to breast cancer
- **Perceived severity** of breast cancer
- **Perceived benefit (response efficacy)** of screening in relation to attitude towards cancer treatment, belief for treatment
- **Perceived barrier** of uptake of screening ( fear of being cancer positive, fear of discrimination and stigma, perception of confidentiality, previously knowing the provider, time to think over for readiness, perceived knowledge about the service, perception about non acceptance of accompany)
- **Self-efficacy** to have screening and to live with breast cancer.
- **Cues to actions:** Facilitating and triggering a women to uptake of screening
- **Distal variables** (factors emerged from qualitative parts)

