**3.6.3. Outcome measures:**

Outcomes will be compared between intervention and control arms, and between different time points of each arm. The primary outcomes include breast cancer screening behavior/intention (mammography use, breast self-examination and breast clinical exam), secondary outcomes include increased awareness for breast cancer and its screening and developing health motivation. Another outcome is, not a must, community based intervention mechanism using HBM constructs effectiveness. The outcome for qualitative part will be measured with respect to constructs of health belief model and anomalies treated accordingly. If anomalies are there, they will be used in questionnaire amendments to be included in quantitative and treated as distal factors in the conceptual framework.

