## Data Analysis

Qualitative data will be analyzed by Atlas ti.7 software and use narration and direct quotation. For quantitative, analysis at baseline**, e**quivalence of two arms will be analyzed at baseline. The equivalence will be analyzed by using Mann- Whitley U test, Chi-square test, T-test or ANOVA.

**Analysis of intervention outcomes:** Consolidated standards of reporting trials (CONSORT standards) will be followed for reporting in this study [79]. For intervention arm and control arm comparison, indicators of rates of breast screening, breast self-examination and/or breast clinical exam at baseline, after three months and at the end of six months will be compared by using Chi-square and T-test. And logistic regression model will be used for predicting independent predictors of breast cancer screening behavior.

**Intention-to-treat (ITT):** Outcome will be analyzed under the basis of ITT. First, the principles of ITT will be applied to test the effects of attrition [80], which means that all participants who have been randomized will be included in the analysis. Missing endpoints will be imputed by using the Expectation- Maximization (EM) algorithm. To gauge the robustness of the outcomes, this analysis will be repeated while using Multiple-Imputation approach. Second, propensity score analysis will also be used. By using logistic model (1 for screening uptake and 0 for not) to predict the probability of be in breast screening behavior. And then use the predicted variable to replace the attrition of dummy variable.

Analysis of intervention mechanism in correlation analyses between each aspect of participants’ community based intervention adoption/use behaviors (e.g. frequency of breast screening by mammography, breast self-examination and/or clinical exam) and effectiveness of the intervention will be performed. A causal path model will be built according to correlation analyses results and related theories. And a path analysis will be subsequently conducted so as to calculate the residual path coefficient and determination coefficient, define causal relationships between different variables, and thus explore intervention mechanism of the community based intervention.

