## 3.12. Strengths of this study

- This is one of the first cluster randomized controlled trials in Ethiopia to implement community based intervention beyond conventional observational studies particularly cross-sectional study.
- The other strength of the study is the research team used qualitative method and other relevant reviews before designing and development of intervention. The intuitively known scholars are participated in this research through development of intervention mapping and modules.
- This will be the first study of its kind in Ethiopia to design and evaluate community based intervention on breast screening uptake. It may help the researchers to recognize the value of interventions and explore new intervention mechanism with an accurate method rather than the mere description of the problem.

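### Section 3.9's only named measure of intervention adoption is the primary outcome behaviour, so if effectiveness means screening uptake, the correlation is largely built in

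*Protocol*

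**What the plan says.** The mechanism paragraph that closes section 3.9 (Data Analysis) of the protocol has two steps. First, it plans correlations between each aspect of participants' adoption or use of the intervention, for which the example given is "frequency of breast screening by mammography, breast self-examination and/or clinical exam", and the effectiveness of the intervention. It names no other adoption measure and does not define effectiveness. Second, "A causal path model will be built according to correlation analyses results and related theories". A path analysis on that model is then to "define causal relationships between different variables" and in this way explore how the intervention works.

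The outcome is described elsewhere by the same behaviours. Section 3.6.1 gives as dependent variable "Breast screening behavior/ uptake (breast self-examination, mammography use, clinical exam"; section 3.6.3 says "The primary outcomes include breast cancer screening behavior/intention (mammography use, breast self-examination and breast clinical exam"; and the participant flow chart (Fig 3) names the main outcome as "Screening Uptake". An earlier paragraph of 3.9 compares the arms on rates of screening by these methods at baseline, three months and six months.

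The intervention itself is something else: an education session every 15 days over three months (3.7.2.2), supported by posters and brochures (3.7.2.5). The control group does not receive it (3.7.2.3). Section 3.6.3 treats the mechanism as an optional outcome. Section 3.12 lists among the strengths that the study may help to "explore new intervention mechanism with an accurate method rather than the mere description of the problem".

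**The concern.** Adoption of an intervention should record how much of it a woman took up. Screening frequency records how far she shows the behaviour that the intervention is meant to change. A control woman who examines her own breasts would count as an adopter of education that she never received.

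If effectiveness is then read as screening uptake, the analysis correlates the number of times a woman screened with whether that number is above zero. Such a correlation appears in any population that contains both screeners and non-screeners, and it carries no information about the education.

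What is at stake is the reading of the mechanism result. A large coefficient produced by overlapping measures could enter the path model and be reported as the way the intervention works. The question that the theoretical framework poses would go unanswered: does the education shift the Health Belief Model (HBM) constructs, and do these in turn shift screening?

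**Working it through.** The protocol gives no figure for this analysis, so there is none to reproduce. The check sets the two sides of the correlation next to each other and then asks how large the correlation is when the intervention has no effect.

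**1. Content of the two sides**

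| Item | Place | Behaviours |
|---|---|---|
| Adoption (only example) | 3.9 | how often: mammography, self-examination, clinical exam |
| Dependent variable | 3.6.1 | uptake: the same three |
| Primary outcome | 3.6.3 | behaviour or intention: the same three |
| Main outcome | Fig 3 | screening uptake |

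**2. Closed form**

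Let X be a woman's screening count and U = 1 if X > 0 her uptake, both from the same visit. Assume X is Poisson with mean m, identical in both arms (the distribution and the means are assumptions, not from the protocol).

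- Cov(X, U) = m − m(1 − e^−m) = m·e^−m
- Var(X) = m; Var(U) = e^−m(1 − e^−m)
- Corr(X, U) = √[ m·e^−m / (1 − e^−m) ]

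| m | Uptake, 1 − e^−m | Correlation |
|---|---|---|
| 0.5 | 39% | √(0.3033/0.3935) = 0.88 |
| 1 | 63% | √(0.3679/0.6321) = 0.76 |
| 2 | 86% | √(0.2707/0.8647) = 0.56 |

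**3. Simulation with the trial's layout**

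From section 3.5: 810 women, 30 kebeles, 15 per arm, hence 810/30 = 27 women per kebele on average. Assumed: no intervention effect; intracluster correlation 0.02; uptake 10%, 30%, 50% or 77.6% (the last is the baseline figure in the sample size calculation); count among screeners equal to 1 plus a Poisson variable, with mean count 1.5, 3 or 6; 300 runs per scenario.

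- Frequency with uptake: average correlation 0.71 to 0.93, significant in every run, both in all 810 women and in the 405 intervention women alone.
- Arm with uptake: average correlation between −0.004 and 0.003.

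The two ends can be checked by hand. With uptake π, mean count among screeners μ and variance v = μ − 1, the correlation is √[ (1 − π)μ² / (v + (1 − π)μ²) ].

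- π = 0.776, μ = 1.5: 0.224 × 2.25 = 0.504; √(0.504/1.004) = 0.71.
- π = 0.10, μ = 6: 0.90 × 36 = 32.4; √(32.4/37.4) = 0.93.

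**4. If effectiveness is a secondary score instead**

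This was simulated in 405 women, again without any effect of the intervention on either variable.

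| Relation of score to frequency | Average correlation | Runs significant |
|---|---|---|
| Unrelated | 0.00 | 6% |
| Weak common cause (such as motivation) | 0.04 | 13% |
| Stronger common cause | 0.15 | 88% |

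**The case against.** Several points can fairly be made for the protocol.

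- *Screening frequency is an example.* A reader might infer that the protocol defines adoption as screening frequency. It does not: the wording leaves the list open. This stands. Still, frequency is the only measure named, and an analyst who follows it meets the overlap.
- *Effectiveness is undefined.* A reader might infer that a strong mechanism is bound to appear even if the education does nothing. The text does not support that. Fig 3 and 3.6.3 list secondary outcomes such as knowledge, attitude, awareness and health motivation, and 3.6.3 links the mechanism outcome to the HBM constructs. With such a score the artefact shrinks or vanishes (step 4). This stands and makes the point conditional.
- *Theory also shapes the path model.* A reader might infer that the model is picked from the correlations alone. Section 3.9 names theory as well, and Chapter Two with Fig 1 sets that theory out in advance. A model that included randomised arm would also show an arm path near zero under no effect. This stands in part: theory does not remove the overlap, and 3.9 does not say that arm is in the model.
- *The analysis is optional and partly worded as exploration.* This stands and limits the weight of the point. The remark in 3.12 is hedged, contrasts the trial with descriptive studies and does not clearly refer to the path analysis, so little rests on it. Exploration is, however, hard to square with "define causal relationships between different variables".
- *Timing, baseline adjustment and clustering of the path model may be in a statistical analysis plan.* This stands. Data at baseline, three and six months allow an ordered model, and the protocol's silence on these details is not counted against it.
- *The correlations are generic.* They rest on assumed counts measured at the same visit. They illustrate the overlap and do not forecast this trial's result.

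**Conclusion.** The point holds in conditional form. The one adoption measure that 3.9 names is the primary outcome behaviour. If effectiveness is measured by screening uptake, which is the natural reading because uptake is the main outcome, the planned correlation is largely built in. Its size is about 0.56 to 0.88 for Poisson counts with mean 2 down to 0.5, and 0.71 to 0.93 under the second set of assumptions, with no intervention effect in either case. Both ranges assume that frequency and uptake come from the same visit.

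A path model that rests partly on such correlations cannot settle what causes what. A reader might also infer that the trial's main result is compromised. It is not: the comparison of the randomised arms on screening does not use the adoption measure. The flaw is confined to an optional mechanism analysis. It is more than a missing detail, because following the stated example would give a misleading answer.

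**What to change.** Change section 3.9 in four places.

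1. Remove screening frequency as a measure of adoption. Use exposure to the education instead: number of scheduled sessions attended and materials received, in the intervention arm only.
2. State which variable stands for effectiveness in the mechanism analysis, and keep it separate from adoption.
3. Base the path model on the Fig 1 framework, with randomised arm added as a node: arm to HBM scores at 3 months to uptake at 6 months, adjusted for baseline score and baseline uptake and allowing for clustering by kebele.
4. Replace the claim to establish causal relationships with exploratory wording. Only the arm is randomised. Attendance and HBM scores are not, so their links with uptake can still reflect common causes such as motivation.

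The cost is small. The HBM scores and screening behaviour are already to be collected at baseline, 3 and 6 months (3.7). What is new is a simple attendance record: section 3.7.2.2 has women register names and phone numbers, but for tracking and reminders, not for attendance. Sessions every 15 days over three months amount to about six per woman (90/15, taking three months as 90 days).

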## Anticipated Limitations

- One limitation of this study is that the control group received a usual intervention which may confound the intervention given in intervention arm. Health extension workers may be motivated more than usual time to teach them after the start of this research.
- Another limitation of this study is that the study used health promotion intervention at community level which by far used to reach unreached community, in case information contamination may exist due to the nature health promotion research.

## 3.12. Strengths of this study

- This is one of the first cluster randomized controlled trials in Ethiopia to implement community based intervention beyond conventional observational studies particularly cross-sectional study.
- The other strength of the study is the research team used qualitative method and other relevant reviews before designing and development of intervention. The intuitively known scholars are participated in this research through development of intervention mapping and modules.
- This will be the first study of its kind in Ethiopia to design and evaluate community based intervention on breast screening uptake. It may help the researchers to recognize the value of interventions and explore new intervention mechanism with an accurate method rather than the mere description of the problem.

